### Study goals and objectives

The study has an overall aim to determine the effects of 24 weeks self-directed activity combined with motivational interviewing on (i) psychological health (depression, anxiety, stress), (ii) quality of life (QoL; physical, social/family, emotional and functional) and (iii) immune function in female breast cancer survivors. In addition, we will explore the dose-response relationship between exercise volume (step count) and the outcome measures.

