## Methods of intervention

### Self-directed physical activity

Participants will perform a 24-week period of self-directed, pedometer controlled physical activity [38, 39]. All participants will be given a step-count tracker devise (Fitbit Alta HR) and investigators will explain the prescribed pedometer-based activity to participants. Fitbit Alta HR is a wearable gadget and can be used to monitor step count. The participants’ activity engagement will be accompanied by individual face-to-face and phone call MI [22]. Participants will be taught how to operate the Fitbit and will be taken on a 10 min walk to experience a moderate level of exertion.. At week 1 (baseline or T1), all participants will be prescribed to assess and record their activity using the Fitbit monitoring device through its application via computer or smartphone to establish their baseline physical activity volume by step count. Following this, they will be advised to perform their activity on their own pace as tolerated and will wear the Fitbit during the daytime or when they are available for physical activity throughout the 24 weeks. Individual participants will be advised and motivated to gradually increase their daily steps on physical activity at moderate intensity exertion or at their perception of taking some efforts but can talk during physical activity (the recommendation by the department of health, Australian government) [40] during face-to-face and over the phone MI. The participants will be advised for safety during physical activity. They will be suggested to stop physical activity if adverse symptoms occur such as chest pain or pain down to arms, dizziness, difficulty breathing, unusual rapid heart rate, and sever fatigue. The researcher will suggest to the participant to inform their family members and take a mobile phone with them before they go out to exercise. They will be also advised to take record of their daily steps in their notebook. All participants will be informed that the researcher will track the participants’ step count and tracker usage time via Fitbit connect application. Individual average daily step count, and activity level will be assessed at baseline (T1), week 12 (T2), and week 24 (T3).

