#### Secondary outcomes

##### Average daily step count

Participants will record their own daily steps through the Fitbit Alta HRapplication, upload their step count on their computer or smartphone and send the data to the researcher by email or phone call weekly. They can also record their steps from the tracker in a provided notebook. Researchers can track an individual’s daily step count via Fitbit Alta HR application on a computer or smartphone. The average daily step count will be calculated at baseline at each of the 12 weeks of the intervention program.

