#### Analysis of data

Baseline descriptive statistics (mean, standard deviation for continuous data and percentage for categorical data) will be used to describe the distribution of personal data and variables between two groups of participant (e.g., age, breast cancer health history, body compositions, and blood pressure). Independent T-test will be used to compare means for continuous data and the Pearson Chi square will be used for testing the difference in distribution of a categorical variable at baseline [49].

Linear-mixed models will be used to identify the relationship between physical activity volume by step counting and mental health (DASS-21), QoL (FACT-B), self-regulation (BREQ2) and self-efficacy at T1, T2 and T3; the relationship between activity volume by step counting and immune biomarker changes at T1,T2, and T3. The models will also be used to control for the effect of covariates or confounding factors and to manage for missing data.

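### The mixed models said to manage missing data do so only for missing outcomes; a visit with no usable step count, the predictor, is dropped

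*Protocol article*

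**What the plan says.** The Analysis of data section names one type of model for the outcomes: "Linear-mixed models will be used to identify the relationship between physical activity volume by step counting and mental health (DASS-21), QoL (FACT-B"), continuing with BREQ2 and self-efficacy, and a parallel model for the immune markers, all at T1, T2 and T3. The Methods paragraph of the Abstract describes the same models and adds that they are between the two groups. The section closes with the missing-data statement: "The models will also be used to control for the effect of covariates or confounding factors and to manage for missing data". It names no other method for missing values.

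The direction of the relationship comes from Study goals and objectives: "we will explore the dose-response relationship between exercise volume (step count) and the outcome measures". Step count is the dose and the questionnaires and immune markers are the response. Under Self-directed physical activity and in Table 1, step count is assessed at all three time points, so it varies over time within a participant.

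Three statements bear on whether step values will be present. Participants "will wear the Fitbit during the daytime or when they are available for physical activity throughout the 24 weeks". They upload their counts and "send the data to the researcher by email or phone call weekly". Wearing time with data capture is itself a secondary outcome (Adherence in step tracker usage). There are also back-ups: a notebook for daily steps, and tracking by the researcher through the Fitbit application (Self-directed physical activity; Average daily step count).

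**The concern.** A likelihood-based linear mixed model uses every observed outcome and is valid if outcomes are missing at random given what is in the model. It conditions on its predictors and has no distribution for them, so a row without a step value adds nothing to the likelihood, even when the DASS-21, the FACT-B and the blood sample were all obtained. For step count, the stated safeguard becomes complete-case analysis.

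Two things are at stake. The first is precision, because attended visits are discarded. The second is bias, if participants with poor mood or motivation at a visit are less likely to have worn the device in that window. The score that would explain the missing steps is then on file, but deleting the row discards it. The article's own Discussion makes such a link plausible. It expects those who adhere to be more intrinsically motivated and to have higher self-efficacy, adherence is defined by tracker wear, and motivation and self-efficacy are outcomes in these models.

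**Working it through.** **Inputs from the article.** 64 participants and three time points (Sample size estimation and justification; Table 1), so 64 × 3 = 192 planned person-visits: 64 at baseline and 128 after it. Drop-out is 10–20% of participants (same section).

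**Inputs assumed.** The article gives no rate of missing step averages, so there is no stated figure to reproduce. I take m = 10–30% of attended post-baseline visits, complete baselines, and all drop-out before T2.

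**Step 1: does the model drop the visit?** A linear mixed model was fitted to 192 simulated rows with every outcome present and 20 step values missing. It used 172 rows, and 192 − 20 = 172, so all 20 visits were lost.

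**Step 2: how many person-visits are used?** Participants who drop out lose outcome and steps together, so missing steps cost extra rows only at attended visits. With drop-out d, rows used = 64 + 128(1 − d)(1 − m). The percentage of 192 lost is in brackets.

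| Drop-out d | m = 0 | m = 10% | m = 20% | m = 30% |
|---|---|---|---|---|
| 10% | 179.2 (6.7%) | 167.7 (12.7%) | 156.2 (18.7%) | 144.6 (24.7%) |
| 20% | 166.4 (13.3%) | 156.2 (18.7%) | 145.9 (24.0%) | 135.7 (29.3%) |

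The m = 0 column is what the model would use if only outcomes were missing: 7–13% lost. With missing steps the loss is 13–29%. The part due to steps alone is 128(1 − d)m/192. It runs from 128 × 0.8 × 0.1/192 = 5.3 points to 128 × 0.9 × 0.3/192 = 18.0 points.

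**Step 3: does the loss bias the result?** This was simulated with 300 replicates of 64 participants and three visits, a true step slope of 0.30, no true T3 effect, and a random intercept. All parameters are assumed.

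- Steps missing completely at random at 25% of post-baseline visits: about 160 rows used, slope 0.30 (unbiased), standard error up from 0.047 to 0.052.
- Steps missing more often when the outcome at that visit was poor: about 152 rows used, slope 0.27, and a T3 visit coefficient of +0.23 where the truth is zero (−0.01 with full data).

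Random loss costs precision only. Outcome-dependent loss attenuates the slope modestly, by about a tenth here, and distorts the visit term more.

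**The case against.** The strongest reply is that managing missing data by a mixed model is ordinary shorthand, true for outcomes, and that the treatment of device data and valid wear days belongs in a fuller plan. That stands as far as detail goes: the article does not rule out imputation, and its absence here is not the point. The point is that the article names a mechanism, in the sentence after it describes models built on step count, and that mechanism does not work for step count.

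The back-ups also count. The variable is an average, so it is wholly missing only when no usable day exists in the window, and the notebook and researcher tracking cover failures to send data. They cannot supply steps for days when the device was not worn. Partial wear mostly produces measurement error, which is a different problem.

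The word relationship does not by itself make step count the predictor. The dose-response wording in the objectives does. If step count were the dependent variable, the same deletion would fall on visits with missing questionnaire or immune values.

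A reader might also infer four stronger claims that the documents do not support:

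- **A loss of 19–44%.** This comes from treating drop-out and missing steps as independent at every visit, baseline included: 1 − 0.9 × 0.9 = 19% and 1 − 0.8 × 0.7 = 44%. The stated 10–20% is participant drop-out, which does not remove baselines.
- **Bias because low-activity visits go missing.** Missingness that depends only on the predictor leaves a correctly specified complete-case slope unbiased.
- **Step count as the variable most likely to be missing.** The article does not say so; questionnaires and blood draws can be missed too.
- **Bias in every primary-outcome comparison.** The objectives introduce the dose-response analysis as an addition to the main aim. A between-arm model without step count would be untouched.

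**Conclusion.** The concern holds in limited form. The claim that the mixed models manage missing data is correct for outcomes under missing-at-random and incorrect for step count, the predictor in the outcome models that the article describes. On the assumptions above, about 13–29% of the 192 person-visits would be lost instead of 7–13%. The upper end depends on an assumed 30% of attended later visits lacking steps, and the true rate cannot be known from the article. Bias is possible but not shown. It requires missing steps to depend on the outcome given the predictors, and its size in the simulation reflects chosen parameters. The point is worth correcting before analysis, but it does not undermine the trial.

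**What to change.** Make three changes to the analysis text.

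1. Estimate the between-arm effects on DASS-21, FACT-B and the immune markers from a mixed model with randomised arm, visit and their interaction. It needs no step data and uses every visit with an outcome.
2. For the step-count (dose-response) models, multiply impute missing step averages from arm, visit, other weeks' steps, wear time and the outcomes. Report the complete-case analysis as a sensitivity analysis. The two fail under different conditions: imputation if missingness depends on the unseen steps themselves, complete-case if it depends on the outcome. Showing both is therefore informative.
3. Limit the statement that the mixed model manages missing data to missing outcomes under missing-at-random.

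The cost is about one paragraph and some extra analysis, with data the trial already plans to collect. The downside is that an imputation model must be specified in advance and rests on missing-at-random.

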#### Data security and confidentiality

The patient’s personal information and health history which are necessary for this research study will be protected for their privacy and confidentiality [50]. All data of participants will be recorded adequately and stored in a secure, password protected databank Agreements involving data ownership and storage will be done between Western health and Victoria University. This study has planned to hold clinical trials research data for 15 years or more based on circumstances [36]. It is possible to keep files of hard copy and electronic files in a research office at Sunshine Hospital. A locked filing cabinet and a computer for research data can only be accessed by agreed members of the research team. More specifically, the researchers will have a backup or reserved storage [36]. For destruction of the data, hard copy will be shredded by hospital and university office’s shredder. Digital information will be destroyed by deleting or overwriting the files. According to the protection of participants’ privacy, personal, health related data and clinical outcomes will be kept and reported in coded or reversibly anonymised technique. Re-identifiable information will be used for data management (name will be removed and replaced by a code which can be re-identified for relating the different data sets and data verification) [36].

## Discussion

Self-directed physical activity in this clinical trial is considered a feasible practice in breast cancer survivors. More specifically, the combination of self-monitoring (step count) and MI have been shown to be important strategies for long-term adherence to physical activity behaviour in people living with cancer. This trial, will examine the efficacy of these health behaviour change techniques in self-directed physical activity. This is an important issue because this is a potentially low cost intervention which could be applied and implemented widely if successful. This study is guided by the Self-Determination Theory [32] and Social Cognitive Theory [26]. We anticipate that those who adhere to the program will be more intrinsically motivated at the end of the trial in comparison to those who do not. We will also explore whether the initial motivational orientation predicts adherence to the physical activity program. In addition, we would anticipate that successful adherence to the physical activity program will be associated with higher levels self-efficacy believes and reduced number of barriers to be physically active.

The primary outcomes of this study focuses on both psychological and physiological changes which can translate positively for their breast cancer clinical outcomes. The study expects the enhancement of their QoL, psychological health and immune biomarkers in 12 to 24 weeks self-directed physical activity by pedometor application combining 12 weeks motivational interviewing.

## Data Availability

Study materials as well as datasets or analysed data during the current study are available from corresponding authors for all acceptable requests.

## Abbreviations

PAPHIO study: Physical activity adherence psychological health and immunological outcomes study
QoL: Quality of life
IIG: Immediate intervention group
DIG: Delayed intervention group
BREQ2: The behavioral regulations in exercise questionnaire version 2
DASS21: A 21-item depression, anxiety and stress scale,
FACT-B: the Functional Assessment of Cancer Therapy-Breast
ANOVA: analysis of variance
MI: Motivational interviewing
PBMC: Peripheral blood mononuclear cell
ES: Effect size
HREC: Human research ethics committee
CD: Cluster of differentiation
